### Treatment and assessment schedule (participant timeline)

The study period will run from approximately 5 weeks’ gestation until 3 days after birth. The duration of the self-efficacy theory-oriented antenatal PA program will be from approximately 13 to 14^+6^ weeks’ gestation until 35–37 weeks’ gestation. To assess the comparability of the study groups, sociodemographic and baseline clinical data will be obtained from the hospital database and pregnant women. The first follow-up will be conducted at 24–27^+6^ weeks’ gestation, and the second and third follow-ups will be performed at 35–37 weeks’ gestation and within 3 days after giving birth. Figure 1 outlines the process of the study.

**Fig. 1 Fig1:**
[figure not shown]
Pragmatic randomized controlled trial flowchart

### Intervention

Bandura’s self-efficacy theory [29, 30] guided the development of our self-efficacy-enhancing PA intervention to increase PA self-efficacy in women with high-risk factors for gestational diabetes mellitus; to decrease their incidence of GDM and blood sugar values; and to improve their PA level, proper gestational weight gain, maternal outcomes, and neonatal outcomes.

The intervention will start between 13 and 14^+6^ week’ gestation and will last for 24 weeks. After recruitment, about 8–10 pregnant women with similar expected dates of confinement will be included into a small group. The intervention will be conducted with the combination of face-to-face and online methods in small groups. The self-efficacy-enhancing intervention is complex.

The intervention includes the following components: (1) one 40-min face-to-face education session regarding GDM, healthy pregnancy weight gain, and PA during pregnancy conducted by an obstetric nurse and midwife; (2) one 50-min face-to-face exercise clinic visit conducted by a coach, obstetrician, nurse and midwife; (3) one 40-min daily exercise video including aerobic, resistance, and stretching exercises delivered to the women through WeChat platform (Tencent, Shenzhen, China); (4) daily reminders via the WeChat group to encourage the women to follow the 40-min video, performing the exercises and recording in their exercise diary; (5) one 40-min face-to-face education session regarding self-management of pregnancy-related symptoms conducted by an obstetric nurse and midwife; (6) one 40-min online education session regarding pregnancy-related emotion management conducted by an obstetric nurse, midwife and psychological consultant via Tencent Meeting (Tencent, Shenzhen, China); and (7) six offline and five online group discussion follow-up sessions (30–40 min for each session) every 2 weeks via Tencent Meeting or WeChat delivered by an obstetric nurse and midwife.

The initial face-to-face intervention will be delivered at the antenatal clinic of the study hospital during 13–14^+6^ weeks’ gestation. This first education session will focus on providing knowledge regarding the necessity and security of exercise during pregnancy. A booklet with the knowledge will be provided to participants. After the education session, the coach will conduct a face-to-face group exercise clinic visit to teach the pregnant women how to exercise safely under the supervision of obstetricians, nurses, and midwives. The coach will discuss the steps participants can take to help them begin exercising. For example, participants could ask their friends and family members to join them in activities like brisk walking instead of more sedentary activities, or begin by completing 10 min of moderate PA daily and increasing this amount gradually to 30 min. Additionally, the coach will guide the participants to exercise together following the exercise video.

The exercise video lasts for 40 min, including a 5-min warm-up, 30-min main exercise section, and a 5-min cool-down. The movements in the exercise video have been recommended by the coach. The warm-up and cool-down sessions contain stretching exercises for the arms and legs at a light intensity. The main section includes aerobic exercises (walking briskly) and resistance (bodyweight) training at a moderate intensity. Aerobic and resistance exercises will be repeated 10–15 times for each movement. The moderate intensity of the exercises will be set according to each woman’s perceived effort (within the range of 12–14 points on the Borg Scale) [44] and Talk Test (one can talk but not sing during exercise) [45]. Participants can adjust the exercise intensity and frequency according to the progress of their pregnancy.

The exercise video will be uploaded to the WeChat platform, a free application released in 2011 by Tencent. With its convenience and various services, including instant messaging, free phone calls, group discussion, sharing moments, mobile payment, small programs, and public accounts, WeChat has become the most prevalent social networking platform in China. The latest data from the 2020 Social Media User Behavior in China report indicates that 88.1% of WeChat users open their WeChat app every day, including 53.9% who do so for > 2 h per day [46]. We will advise the women to exercise at home following the exercise video for ≥ 5 days a week. Researchers will remind the women to exercise and record exercise diaries every day through the WeChat group.

An offline group discussion at the antenatal clinic of the study hospital or online group discussion via Tencent Meeting will be delivered by an obstetric nurse and midwife every 2 weeks. These sessions will aim to strengthen participants’ self-efficacy in PA and will be guided by a protocol. Pregnant women in small groups will sit around to discuss the problems that arise when doing exercise and share solutions on how to keep active with each other. Researchers will analyze the group members’ gestational weight gain and PA status in the prior 2 weeks. Feedback will be given to every group member. The nurse will provide encouragement and reinforcement of the participants’ efforts and successes and will empower them through support. Successful pregnant women will be invited to share their self-management strategies as role models. The duration of each group discussion session will vary from 30 to 40 min according to group members’ needs.

During 15–16^+6^ weeks’ gestation, face-to-face knowledge education about pregnancy-related symptom management will be provided by obstetric nurses and midwife at the antenatal clinic of the study hospital. After that, an offline group discussion will be held at the antenatal clinic of the study hospital. During 17–18^+6^ weeks’ gestation, online knowledge education about pregnancy-related emotion management will be offered by an obstetric nurse, midwife and psychological consultant online via Tencent Meeting. A group discussion will be held online after the knowledge education session by an obstetric nurse.

The four strategies recommended by Bandura [29] were incorporated into each component of the intervention. Accomplishment experiences include identifying potential barriers and discussing self-management strategies for being physically active every day, goal-setting, the use of the exercise video to practice at home, and the booklet for reinforcing knowledge. Vicarious experiences include participants who had successfully done exercise according to the coach’s guidance sharing their self-management skills to keep active. Verbal persuasion includes providing encouragement and acknowledging participants’ ability to keep themself active. Physiological monitoring includes the explanation for why symptoms and negative emotions might occur during pregnancy, and the discussion of management strategies. Table 2 outlines examples of the four strategies [29].

**Table 2 Tab2:** Strategies used in the self-efficacy-enhancing intervention

Performance accomplishments	Identifying the obstacles to keeping participants active through discussion
	Setting achievable goals and actions, e.g., achieving 10 min of exercise following the exercise video daily before increasing gradually to 30 min
	Negotiating techniques with participants to achieve bigger goals, e.g., set alarm on phone for activity; put notes on doors, the refrigerator, or the television to be active; stand or walk rather than sitting in add breaks
	Monitoring physical activity diary and gestational weight gain on WeChat notes
	Planning for decreasing sedentary behavior
	Providing positive feedback for participants’ accomplishments
	Providing booklet to reinforce knowledge
Vicarious experience	Checking behavioral tracking, review, and feedback on goals; “we’re going to check how you went with your physical activity and tracking and work together to set a healthy activity goal.”
	Sharing self-management strategies from successful pregnant women
Verbal persuasion	Discussing and providing information about consequences of physical inactivity and unhealthy gestational weight gain
	Confirming participants have the capability for exercise and weight self-management
	Informing that one’s own behavior may be an example to others, i.e., inform the participants that if they do physical activity, that may be a good example for their friends and family members.
	Guiding participants to recall previous successful behavior-change situations, discuss context and factors associated with success
	Providing positive feedback for the participant’s effort
Physiological states	Assessing and explaining the participant’s pregnancy-related symptoms and negative emotions
	Discussing strategies for managing symptoms, anxiety, or depression, such as positive self-talk and muscle relaxation

The intervention will be conducted by a multi-disciplinary team of obstetricians, nurses, midwives, psychological consultant, and coaches, all of whom have had >10 years of experience in their professional field. A 4-h training session will be provided to the team members by the first researcher ([name]) before the study begins. The study protocol will be reviewed and discussed to ensure consistency in delivering the PA intervention.

The Medical Research Council guidelines for the evaluation of complex interventions will be used to explore the process by which the intervention may have led to its effect or not [47]. Multiple methods of data collection will be used to assess the implementation of the intervention, the mechanisms of impact, and context effects (Table 3).

**Table 3 Tab3:** Process evaluation items, indicators, and methods of measurement

Process evaluation items		Indicators	Measurement

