### Sample size

The sample size of this study was calculated based on recent research available on the impact of PA on the incidence of GDM in Chinese overweight and obese pregnant women. Using information from that study [38] documenting incidence rates of GDM of 22% in the intervention group after PA intervention and 40.6% in the control group, we found that a sample size of a ≥ 98 women in each arm of this study will be required to detect a difference in the incidence of GDM between groups (80% power and *α* = 0.05). The treatment and control ratio is 1:1. Allowing for 20% attrition during pregnancy, ≥ 122 women in each arm will need to be recruited.

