### Statistical analysis

All data will be analyzed by SPSS version 26 software (IBM Corporation, Armonk, NY, USA). Descriptive statistics, such as frequencies and percentages of categorical variables and mean, standard deviation, median, and range values of linear variables, will be used. To gain insight into the relative factors of PA, descriptive statistics will be calculated to describe participants’ demographic characteristics, gestational weight gain, PA level, and PA self-efficacy during pregnancy. Primary analyses, including chi-squared and independent *t* tests, will be used to examine group differences in the primary and secondary outcomes. Repeated analysis of variance will be used to assess within-patient correlations. By using a series of mixed-effects regression models with a likelihood-based approach, we will regress the score of PPAQ at follow-up to determine the effect on the baseline, group, time, group × time, and confounders identified in the preliminary step. Effect sizes will be reported with 95% confidence intervals, and results will be considered significant if *P* < 0.05. The analysis of the primary and secondary outcomes will be based on an intention-to-treat basis [59], which will include study withdrawals and losses to follow-up.

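### Intervention women are treated in interacting small groups, but the sample size and the named tests treat every woman as independent

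*Protocol article*

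**What the plan says.** **Delivery.** Women are randomised individually in blocks of four (Randomization and blinding). In the intervention arm, "pregnant women with similar expected dates of confinement will be included into a small group", about 8–10 per group. The group then shares education sessions, a coached exercise visit and two-weekly discussions. In the discussions women exchange solutions, and successful members are presented as role models (Intervention). The Control group section describes customary consultations and no grouping.

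**Sample size.** The inputs are "incidence rates of GDM of 22% in the intervention group after PA intervention and 40.6% in the control group", with "80% power and *α* = 0.05". The result is that "a sample size of a ≥ 98 women in each arm of this study will be required". The section adds: "Allowing for 20% attrition during pregnancy, ≥ 122 women in each arm will need to be recruited". No ICC or design effect appears.

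**Analysis.** The Statistical analysis section says that chi-squared and independent t "tests, will be used to examine group differences in the primary and secondary outcomes". The only correlation it mentions is within-patient. The mixed model planned for the Pregnancy Physical Activity Questionnaire (PPAQ) lists baseline, group, time, their interaction and confounders. Group there means trial arm; no term for the small group is listed.

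**The concern.** This is a partially nested design: women in one arm are treated in groups and women in the other are not. The intervention is meant to work partly through group members influencing one another, since vicarious experience is one of its four named strategies. Independence within groups is therefore hard to take for granted. If members of a group end up more alike than women from different groups, the intervention-arm variance is larger than a chi-squared or t test assumes.

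Two things follow. The tests as planned would reject too often. A valid test would have less power than the sample size section claims. The first matters most, because the Discussion proposes considering the program for regular care if any primary or secondary outcome is positive.

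**Working it through.** **Inputs from the protocol article.** Incidence 0.22 and 0.406; 98 evaluable and 122 recruited per arm; 20% attrition; 1:1 ratio; groups of about 8–10. Two-sided testing is assumed because it reproduces the stated figure.

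**Assumed.** ICC of 0.01 to 0.10, because the documents give none. Nine women are taken per recruited group, so 9 × 0.8 = 7.2 are evaluable. The number of groups is between 122/10 = 12.2 and 122/8 = 15.25.

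**Step 1: reproduce the plan.** With mean rate p̄ = 0.313, p̄(1−p̄) = 0.2150 and arm variances 0.22 × 0.78 = 0.1716 and 0.406 × 0.594 = 0.2412:

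n = [1.96 √(2 × 0.2150) + 0.8416 √(0.1716 + 0.2412)]² / 0.186² = 96.4, so 97 per arm against 98 stated. Power at 98 is 80.7%, and 98/0.8 = 122.5 against 122 stated. The figure is reproduced, and it is an independent-observations figure with no allowance for grouping.

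**Step 2: inflate the intervention arm only.** DE = 1 + (7.2 − 1) × ICC. With equal arms, the null variance of the difference grows by (1 + DE)/2, so:

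- type I error of the planned test = 2[1 − Φ(1.96 / √((1 + DE)/2))]
- power of an adjusted test = Φ[(0.186 − 1.96 × SE0) / SE1], where SE0 = √(0.2150 × (DE + 1)/98) and SE1 = √((0.1716 × DE + 0.2412)/98)
- power of the planned test uses the same SE1, but its critical value uses SE0 with DE = 1.

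**Worked case, ICC 0.05.** DE = 1 + 6.2 × 0.05 = 1.31, and √(2.31/2) = 1.075. Type I error = 2[1 − Φ(1.96/1.075)] = 6.8%. SE0 = 0.0712 and SE1 = 0.0690. Adjusted power = Φ[(0.186 − 0.1395)/0.0690] = Φ(0.674) = 75.0%.

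| ICC | DE | True/assumed null SE | Type I error, planned test | Power, planned test | Power, adjusted test |
|---|---|---|---|---|---|
| 0 | 1.000 | 1.000 | 5.0% | 80.7% | 80.7% |
| 0.01 | 1.062 | 1.015 | 5.4% | 80.4% | 79.5% |
| 0.05 | 1.310 | 1.075 | 6.8% | 79.2% | 75.0% |
| 0.10 | 1.620 | 1.145 | 8.7% | 78.0% | 69.6% |

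**Check of the approximation.** A beta-binomial simulation of the planned test (11 groups of 9 against 98 independent controls, 100,000 runs) gave type I errors of 5.5%, 7.6% and 9.9% at ICC 0.01, 0.05 and 0.10. The formula with 9 per group gives 5.5%, 7.4% and 9.8%, so the two agree closely. All the power figures use a normal approximation. A small-sample correction for 12–15 groups would lower the adjusted power a little further.

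**The case against.** The strongest reply is that the harm is conditional. At ICC 0 the stated power stands, and at 0.01 the effect is trivial: 5.4% type I error and about one point of power. Several features may keep the ICC low. There is one centre and one exercise video, discussions follow a protocol, the team is trained together, exercise is done at home, and intensity is set by each woman's own perceived effort. GDM and glucose are measured at 24–28 weeks after a start at 13–14+6 weeks, so only about 9–15 weeks of group contact precede them. The full program precedes only the later outcomes, such as physical activity at 35–37 weeks. All of this stands. It limits the likely size but does not make the named tests suit the design.

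Four stronger readings are tempting, and the documents do not support them:

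- **That standard errors are too small and 80% power is not delivered, as facts.** Both need an ICC above 0, which the documents neither give nor rule out.
- **That the planned tests lose much power.** Their power barely moves (80.4% to 78.0% over the range). The clear loss belongs to a valid adjusted test.
- **That the loss is as large as 9 women per group with 98 evaluable implies** (73.4% at ICC 0.05, 66.7% at 0.10). That pairing ignores attrition. If groups stayed at 9, all 122 would be analysed and power at ICC 0.05 would be 82.4%.
- **That the groups are fixed and each has its own WeChat group.** The article says neither.

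It is also fair that a condensed article may leave the random-effects structure of the PPAQ model to a fuller plan. The point therefore rests mainly on the chi-squared and t tests, which are named outright, and on the sample size.

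**Conclusion.** The concern holds in conditional form. The article describes group delivery in one arm, then sizes the trial and names tests as if all women were independent. If outcomes correlate within groups, the main harm under the plan as written is type I error above 5%: about 5.4% to 8.7% for ICC 0.01 to 0.10. A valid analysis of 98 women per arm would have about 79.5% to 70% power over the same range. These sizes rest on the assumed ICCs, about 7 evaluable women per group, clustering in the intervention arm only, and the plan's own incidence rates. The calculation is for GDM. The same reasoning applies to the glucose, PPAQ and self-efficacy comparisons, whose ICCs are likewise not given and could differ.

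**What to change.** 1. Record each intervention woman's small-group identifier in the intervention logbook, which Table 3 already lists.
2. In Statistical analysis, replace the chi-squared and independent t tests with a partially nested analysis. Either fit a random intercept for small group in the intervention arm only, with controls as singletons, or use cluster-robust variance. Apply a small-sample correction for about 12–15 groups.
3. Use a logistic model for GDM and linear mixed models for glucose, PPAQ and the Pregnancy Exercise Self-efficacy Scale. Arm-specific residual variance belongs in the linear models only, since a logistic model has no residual variance to vary by arm.
4. In Sample size, state an assumed ICC and give power conditional on it: about 79.5% at ICC 0.01 and 75% at 0.05.

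**Cost.** One extra variable, revised analysis wording, slightly wider intervals and a less favourable power figure. No extra patients are needed. The change makes the inference valid and the power statement honest; it does not restore 80% power.

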**Implementation**			
Dose	Quantity of the intervention implemented	Number of sessions received Frequency and duration of exercising with the exercise video	Intervention logbook; WeChat record
Reach	How well the intervention is received	Percentage of pregnant women who met the inclusion criteria attend this study Percentage of participants who completed the intervention	Intervention logbook; WeChat record
Fidelity	Whether the intervention was delivered to participants according to the protocol	If the session was delivered to participants, gestational weeks, begin-time, complete-time; if the session was completed, reasons for participation and declining participation	Intervention logbook; WeChat record; semi-structured interviews
Adaptation	Extent to which adaptation across contents is acceptable	Satisfactory rate	Satisfactory questionnaire; Semi-structured interviews
**Mechanism of impact**			
Participant responses	Participant responses to and interactions with the intervention	How satisfied are participants with the content, work procedures, and delivery? What is their opinion of the physical activity program’s appropriateness/usefulness, acceptability, feasibility, sustainability?	Satisfactory questionnaire; Semi-structured interviews
**Context**	Which factors/circumstances have either facilitated or hindered working with the interventions?	Which factors/circumstances have either facilitated or hindered working with physical activity programs?	Semi-structured interviews.

Adherence to the PA intervention will be strongly emphasized and registered in the women’s training diaries and reports from the individuals leading the training groups. Exercise participants who develop obstetric contraindications to exercise [18] will discontinue the exercise intervention but be included in the intention-to-treat analysis.

### Control group

Participants in the control group will receive the customary regular consultations with the midwife, nurse, or obstetrician. They will not be discouraged from exercising on their own. Neither group will receive special recommendations about diet or other standard antenatal care delivered through prenatal health education.

### Outcome measures and data collection

The list of data-collection instruments and times of data collection are presented in Table 4. The primary outcomes of this study are blood sugar values during the 75-g oral glucose tolerance test, the incidence of GDM at 24–28 weeks’ gestation, and PA levels at 24–28 and 35–37 weeks’ gestation. The secondary outcomes include PA self-efficacy, gestational weight gain, maternal outcomes, and childbirth outcomes.

**Table 4 Tab4:** Data collection instruments and time of data collection

	Booking		24–28 weeks’ gestation		35-37 weeks’ gestation		Within 3 days after delivery	
	IG	CG	IG	CG	IG	CG	IG	CG
**Primary outcomes**								
Blood sugar value on 75-g OGTT (medical database); incidence of GDM			√	√				
PA level (PPAQ)	√	√	√	√	√	√		
**Secondary outcomes**								
PA self-efficacy (P-ESES)	√	√	√	√	√	√		
Gestational weight gain (questionnaire)	√	√	√	√	√	√		
Maternal outcomes (medical records)					√	√		
Neonatal outcomes (medical records)							√	√

*Abbreviations*: *CG* Control group, *GDM* Gestational diabetes mellitus, *IG* Intervention group, *OGTT* Oral glucose tolerance test, *P-ESES* Pregnancy Exercise Self-efficacy Scale, *PA* Physical activity, *PPAQ* Pregnancy Physical Activity Questionnaire

According to the guidelines for the management of gestational diabetes mellitus in China [48], pregnant women with a fasting glucose level of ≥ 7.0 mmol/L or random blood glucose level of ≥ 11.0 mmol/L in early pregnancy are diagnosed with pre-gestational diabetes mellitus. Women who are not diagnosed with pre-gestational diabetes mellitus will receive a 75-g oral glucose tolerance test at 24–28 weeks’ gestation. Using the criteria of the International Association of Diabetes and Pregnancy Study Groups, GDM will be diagnosed when the fasting plasma glucose value is greater than the following standards: 5.1 mmol/L, 10.0 mmol/L in 1 h, or 8.5 mmol/L in 2 h [49].

PA will be measured by the Pregnancy Physical Activity Questionnaire (PPAQ) [50]. Research has shown that PPAQ is reliable and currently the best-available tool to assess PA during pregnancy [51]. The original version of the PPAQ contains 32 items to assess household/caregiving activities (13 items), occupational activities (5 items), sports/exercise activities (8 items), transportation activities (3 items), and physical inactivity (3 items) [50]. For each item, participants select a category of the amount of time spent carrying out the specific activity ranging from 0 to ≥ 6 or ≥3 h/day or 0 to ≥ 3 h/week. According to the calculation guideline of PPAQ [50], each item refers to a given metabolic equivalent of task (MET) value, which describes the PA levels measured in metabolic equivalents. Subsequently, the amount of time spent when carrying out each activity is converted into the MET value. According to the MET value, the total 32 activities could be divided into sitting (< 1.5 METs), low-intensity activity (1.5–2.9 METs), moderate-intensity activity (3.0–6.0 METs), and high-intensity activity (> 6.0 METs). The Chinese version of the PPAQ contains 31 items after deleting the item of “holding babies” [52]. The Chinese version of the PPAQ has been demonstrated to have good psychometric properties, with a content validity of 0.94 and test–retest reliability of 0.94.

PA self-efficacy will be measured by the Pregnancy Exercise Self-efficacy Scale (P-ESES) [53], a 10-item instrument where each item is rated on a 5-point Likert scale ranging from 5 points (strongly agree) to 1 point (strongly disagree). Higher scores indicate a greater level of PA self-efficacy. According to the total score of P-ESES, PA self-efficacy will be divided into a high level (41–50 points), medium level (21–40 points), and low level (10–20 points). The Chinese version of P-ESES contains three subscales: four items in the overcome exercise barriers subscale, two items in the overcome emotion barriers subscale, and four items in the overcome support barriers subscale [54]. The Chinese version of P-ESES has been demonstrated to have good psychometric properties, with a Cronbach’s *α* value of 0.80 and test–retest reliability of 0.53.

Gestational weight gain (GWG) will be calculated as the difference between weight measured at the time of inclusion, 24–28 weeks’ gestation, and 35-37 weeks’ gestation. pre-gestational BMI will be calculated using the self-reported pre-pregnancy weight and height [weight (kg)/(height (m))^2^]. According to the Working Group on Obesity in China [55], individuals may be classified as underweight (BMI < 18.5 kg/m^2^), normal weight (BMI 18.5–23.9 kg/m^2^), overweight (BMI 24.0–27.9 kg/m^2^), or obese (BMI ≥ 28 kg/m^2^) according to their BMI. We will measure maternal body weight to the nearest 0.1 kg with a calibrated electronic scale (RGZ-50; SUHONG Medical Instrument, Jiangsu, China) with participants wearing indoor clothing and no shoes. Excessive gestational weight gain will be identified according to the 2009 guideline issued by the Institute of Medicine [56]. GWG will be categorized as inadequate, normal, or excessive GWG by the same guidelines [56]. Here, inadequate GWG will be defined as a bodyweight gain < 11.5 kg for normal-weight women, < 7 kg for overweight women, or < 5 kg for obese women; normal GWG will be defined as a bodyweight gain of 11.5–16 kg for normal-weight women, 7–11.5 kg for overweight women, or 5–9 kg for obese women; and excessive GWG will be defined as a bodyweight gain > 16 kg for normal-weight women, > 11.5 kg for overweight women, or > 9 kg for obese women, respectively.

Maternal outcomes will include gestational hypertension (defined as a blood-pressure elevation [systolic blood pressure > 140 mmHg or diastolic blood pressure > 90 mmHg] at > 20 weeks’ gestation in the absence of proteinuria) [57], preeclampsia (presence of both high blood pressure and proteinuria at 20 weeks’ gestation), premature rupture of membranes (rupture of membranes before 37 weeks’ gestation or at the onset of delivery), postpartum hemorrhage (blood loss > 500 mL within 24 h of delivery), and mode of delivery (vaginal, operative vaginal, or cesarean [elective or emergency]).

Neonatal outcomes will include gestational age at delivery, preterm birth (< 37 gestational weeks), Apgar score, birth weight, birth length, macrosomia (birthweight > 4000 g), low birth weight (birthweight < 2500 g), fetal distress (fetal hypoxia during pregnancy or labor), and amniotic fluid contamination (presence of meconium in the amniotic fluid), number of LGA infants (birthweight > 90th percentile for gestational age), and number of SGA infants (birthweight < 10th percentile for gestational age). Both LGA and SGA will be defined by international standards for sex-specific newborn size for each gestational age based on data from the Newborn Cross-sectional Study subpopulation [58].

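### The plan leaves open whether the P-ESES total or three wide levels are tested, and it does not extend the baseline-adjusted mixed model to this repeated score

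*Protocol article*

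**What the plan says.** In the protocol article, under Outcome measures and data collection, the P-ESES is "a 10-item instrument where each item is rated on a 5-point Likert scale" running from 1 to 5, so the total runs from 10 to 50, and higher is better. The same paragraph then says that "PA self-efficacy will be divided into a high level (41–50 points), medium level (21–40 points), and low level (10–20 points". It also says that "The Chinese version of P-ESES has been demonstrated to have good psychometric properties", citing a Cronbach's alpha of 0.80 and a "test–retest reliability of 0.53". Table 4 lists the P-ESES as a secondary outcome measured in both arms at booking, 24–28 weeks and 35–37 weeks.

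Under Statistical analysis, chi-squared and independent t tests "will be used to examine group differences in the primary and secondary outcomes". The next sentence adds: "Repeated analysis of variance will be used to assess within-patient correlations". The likelihood-based mixed model, with baseline, group, time and group × time terms, is specified for one outcome: "we will regress the score of PPAQ at follow-up". No sentence says which form of the P-ESES is compared between arms, or by which test.

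**The concern.** Two separate features could each cost precision on the construct that the programme is built to change.

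The first is the cut. The middle level covers 20 of the 41 possible totals, so most women may stay in it even if the programme shifts their scores. A chi-squared test on three ordered levels also ignores their order.

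The second is the single-visit comparison. With a retest reliability of 0.53, one reading is a noisy measure of a woman's self-efficacy. Two follow-up readings and a baseline are already being collected. An independent t test uses one reading at a time and makes no adjustment for baseline. The model that would use all three is in the plan but is applied only to the PPAQ.

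The P-ESES is the only listed measure of self-efficacy. A comparison that is weaker than the data allow could leave a real difference undetected.

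**Working it through.** **Inputs from the protocol article.** Score range 10–50; levels 10–20, 21–40 and 41–50; retest reliability 0.53; alpha 0.80; 98 evaluable women per arm (Sample size section); significance at P < 0.05.

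**Inputs that are assumed.** The article gives no P-ESES mean, SD or target difference. I used control means of 25 to 38, SDs of 5 to 8, roughly normal scores and two-sided tests.

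**The plan's own figure.** The 98 per arm is for GDM incidence, 40.6% against 22%, with 80% power. The pooled two-proportion formula, two-sided and without continuity correction, is

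n = [1.96·√(2·0.313·0.687) + 0.842·√(0.406·0.594 + 0.22·0.78)]² / 0.186² = 96.4, so 97.

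This agrees with the stated 98 within rounding. No power figure is stated for the P-ESES, so 98 per arm is simply carried over.

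**Step 1: width of the levels.** Possible totals: 50 − 10 + 1 = 41. Totals in the middle level: 40 − 21 + 1 = 20. With a mean of 30 and an SD of 5, about 95% of women fall in that level.

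**Step 2: total against levels.** For a 0.4 SD difference and 98 per arm, the noncentral-t power of a t test on the total is 0.80. Simulated power (rounded scores limited to 10–50, Pearson chi-squared on the three levels) was:

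| Control mean, SD | t test, total | chi-squared, levels |
|---|---|---|
| 30, 5 | about 0.80 | about 0.17 |
| 30, 6 | about 0.80 | about 0.32 |
| 30, 7 | about 0.79 | about 0.42 |
| 35, 6 | about 0.80 | about 0.47 |
| 38, 6 | about 0.80 | about 0.60 |

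Over the whole grid, repeated runs put the levels at about 0.16 to 0.60 and the total at about 0.80. The levels were weaker in every scenario.

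**Step 3: one visit against two.** Read 0.53 as the share of variance that is true score, with errors independent between visits, and take a true-score effect of 0.5 SD that is the same at both follow-ups.

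- One visit: observed effect = 0.5·√0.53 = 0.364 SD; power 0.72.
- Mean of two visits: reliability = 2·0.53/(1 + 0.53) = 0.693; observed effect = 0.5·√0.693 = 0.416 SD; power 0.83.

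**Step 4: sensitivity to that reading.** If single-occasion reliability were 0.80 (the stated alpha), one visit gives 0.5·√0.80 = 0.447 SD and power 0.88. Two visits give reliability 1.6/1.8 = 0.889, 0.471 SD and power 0.91. The gain then falls from about 11 percentage points to about 3.

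**The case against.** The strongest reply is that the article never plans a chi-squared test on the P-ESES levels. Chi-squared and t tests share one sentence covering all primary and secondary outcomes, many of which are truly categorical (GDM, mode of delivery, preterm birth). The P-ESES has a numeric total to which the t test fits naturally, and the levels may be meant only for description. This stands. A reader might infer that the plan commits to testing the levels, but the text only permits it.

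A reader might also infer that power is halved. The documents support no single ratio: the loss depends on a mean and SD that they do not give. Nor does the 0.53 reliability explain the gap between the two tests, because it weakens the total and the levels alike.

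The repeated analysis of variance is not confined to the PPAQ and could be applied to the total. That stands too, but its stated purpose is to assess within-patient correlations, and the article does not present it as the between-group comparison or mention baseline adjustment for it.

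The retest interval is not stated, so part of the shortfall from 1 may be real change, and alpha is 0.80. Step 4 shows that the gain from averaging is then small. Calling the scale good beside 0.53 is loose wording, but it alters no analysis and would not justify a change alone.

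Finally, an article may leave detail to a fuller plan. That excuses silence. It does not cover this case fully, because the article fixes the division into levels and assigns the mixed model to one outcome by name.

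**Conclusion.** The point holds as a limited improvement to a secondary analysis. The plan defines a three-level form, leaves open whether it or the total is tested, and does not name its most efficient model for an outcome that has the data to support it.

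If the levels were tested, power for a 0.4 SD difference would be about 0.16 to 0.60 rather than about 0.80, subject to the assumed means and SDs. If a single visit were tested, power for a true effect of 0.5 SD would be 72% rather than 83% when 0.53 is all independent error, and 88% rather than 91% if reliability is nearer 0.80. These are two distinct losses.

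The sample size and the primary outcomes are unaffected. The documents do not show that the trial will lose this power, only that the plan as worded allows it.

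**What to change.** Under Outcome measures and data collection, name the continuous P-ESES total (10–50) as the form to be tested, and state that the high, medium and low levels are descriptive only. Under Statistical analysis, add the P-ESES total to the mixed model already specified for the PPAQ, with baseline, group, time and group × time. Report the group effect across the two follow-ups and at each visit, with 95% confidence intervals. Reporting both keeps the visit-specific results in view if the effect differs between 24–28 and 35–37 weeks.

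The cost is a few sentences. No new data, visits or women are needed. The one thing given up is a significance test on the levels.
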